##### Children’s quality of life

The KIDSCREEN-10 Index will assess children’s global quality of life conceptualized as a multidimensional construct covering physical, emotional, social, and behavioral aspects of well-being and functioning [72–74]. Ten items referring to the past week on a 5-point Likert scale ranging from 0 (not at all) to 4 (extremely) will be answered by both the children and parents. An additional item will ask about general health which can be rated as ‘poor’, ‘fair’, ‘good’, ‘very good’, and ‘excellent’. Negatively worded items will be recoded, so that higher scores for all items indicate higher levels of children’s global quality of life. All items will then be sum scored capturing children’s global quality of life. KIDSCREEN-10 has been used in clinical and epidemiological studies in Europe, North and South America, Africa, and Asia, revealing cross-cultural validity [72].

##### Peer violence

The 24-item version of the Multidimensional Peer Victimization Scale (MPVS) [75] will assess children’s experiences of violence by peers using six subscales: physical victimization, verbal victimization, social manipulation, attacks on property, electronic victimization, and social rebuff. Four items for each category referring to the past week will be answered on a 3-point Likert scale ranging from 0 (not at all) to 2 (more than once). The total victimization score will range from 0 to 32 with subscale scores ranging from 0 to 8, whereby higher scores indicate that a child has experienced more peer victimization. Good psychometric properties have been shown for the original 16-item and the 24-item version of the MPVS [75].

##### Adult–child relationship quality

The People In My Life (PIML) [76, 77] will be used to assess the quality of the parent- as well as teacher–child relationship. Nineteen PIML Parent Factor items will assess quality of children’s self-reported relationship with their parents. The Parent Factor items will be assessed separately for the social mother and father. For teacher–child relationship, 15 items of the Teacher/School Factor items will assess the children’s self-reported relationship with their teachers. All items will be answered on a 4-point Likert scale ranging from 0 (Almost never or never true) to 3 (Almost always or always true). Negatively worded items will be recoded, so that higher scores for all items indicate higher levels of children’s global relationship quality. The Parent Factor items are sum scored as indicator of children’s global quality of their relationship to parents. The Teacher Factor items are sum scored as indicator of children’s global quality of the relationship to their teacher. The psychometric properties of the PIML have been shown to be good [77, 78].

In addition, the parents’ relationship to the own child will be assessed by the Child-Parent-Relationship Scale-Short-Form [79]. Parents will answer 15 items on a 5-point Likert scale ranging from 1 (definitely does not apply) to 5 (definitely applies). Validation studies done in different contexts [80, 81] confirmed the validity of the scale.

##### Perceived stress

The children’s self-reported perceived stress will be assessed with the Perceived Stress Scale for Kids [82] consisting of 11 items referring to the past week that are answered on a 5-point Likert scale ranging from 0 (never) to 4 (always). Negatively worded items will be recoded. The items are sum scored. Higher scores indicate higher levels of stress. Studies on the reliability and validity of the scale showed promising results [82].

Parental self-reported perceived stress will be assessed through an adapted version of the Parental Stress Scale [83]. Parents will answer 18 items about the past week on a 5-point Likert scale ranging from 1 (strongly disagree) to 5 (strongly agree). Negatively worded items will be recoded. The items are sum scored. Higher scores indicate higher levels of stress. The scale has been validated in different samples [84, 85].

Teachers’ self-reported perceived stress will be assessed through the Teachers Stress Inventory [86]. 19 items referring to the past week on a 5-point Likert scale ranging from 0 (never) to 4 (always) will be answered by teachers. Negatively worded items will be recoded. The items are sum scored. Higher scores indicate higher levels of stress. Psychometric properties have already been validated in the context of South Africa [87].

##### School climate quality & teachers’ decision making

The School Level Environment Questionnaire [88] will be used to assess school climate and teachers’ decision making based on teacher report. The Affiliation Subscale will assess school climate. Therefore, 7 items will be answered on a 5-point Likert scale ranging from 0 (strongly disagree) to 4 (strongly agree). Negatively worded items will be recoded. The items are sum scored. Higher scores indicate higher quality of school climate. The Participatory Decision Making Subscale [89] will assess teachers’ decision making strategies. Teachers will answer 7 items on a 5-point Likert scale ranging from 0 (strongly disagree) to 4 (strongly agree). Negatively worded items will be recoded. The items are sum scored. Higher scores indicate better decision-making strategies. Promising psychometric results have been shown in the context of the southwestern United States [89] and also with an adapted version in the context of South Africa [90].

##### Teachers’ self-efficacy

The Teachers Sense of Efficacy Scale [91] will assess the self-efficacy reported by teachers. Twelve items asking about how much they as teachers can do in specific situations will be answered on a 5-point Likert scale ranging from 0 (nothing) to 4 (a great deal). The items are sum scored. Higher scores indicate higher levels of self-efficacy. The Teachers Sense of Efficacy Scale has been used in the context of South Africa [92] and has shown to have good psychometric properties [93].

##### Normative beliefs about violence

Normative beliefs about violence are assessed using purpose built items answered by parents and teachers with 4 items. Two items refer to witnessing violence in the past week at school/in the community using a 6-point Likert scale ranging from 0 (never) to 5 (more than 10 times) and two items refer to general thoughts about disciplining children using a 4-point Likert scale ranging from 0 (never OK) to 3 (always or almost always OK). The respective two items are sum scored. Higher scores indicate stronger normative beliefs about violence.

##### Intimate partner violence

Intimate partner emotional, physical and sexual violence will be assessed for female social parents using purpose-built items from a combination of studies [94, 95] and the CTS. Eight items will be answered by ‘yes’ (1) or ‘no’ (0). If ‘yes’ is indicated, follow-up questions on the time frame and frequency ranging from 1 (once) to 3 (many) will be asked. The items are sum scored. A higher score indicates a higher level of intimate partner violence.

#### Process evaluation and qualitative end-line evaluation

##### Qualitative information on the quality and fidelity of the intervention

The quality of the intervention will be assessed through participants’ and facilitators’ assessments of individual sessions and their components and of the perceived facilitator performance, captured through standardized assessment forms as well as FGDs and in-depth interviews. Fidelity and facilitator performance will additionally be assessed through staff observers who will capture whether any session content remained uncovered or was poorly delivered.

##### Qualitative and quantitative information on participants’ engagement with the intervention

Participants’ attendance of each program session and individual session components will be captured based on detailed attendance records. In addition, participants’ engagement in the session will be assessed through standardized assessment forms filled out by participants themselves, facilitators and staff observers. These will assess which components of the intervention were particularly well liked among participants and which ones were perceived as rather challenging/ineffective. Lastly, participants’ engagement with the intervention will further be discussed in FGDs and in-depth interviews.

##### Qualitative information on functioning of intervention and violence reduction

The FGDs and in-depth interview will assess the parents’ and teachers’ perceived improvements in their use of alternative discipline strategies and the potential reduction in violence against children after their participation in the intervention. The FGDs and in-depth interviews will also be set up to elicit possible mechanisms and barriers of change.

#### Measures against *bias*

The risk of bias will be minimized and the validity of the findings will be increased through several methodological strategies. First, randomly sampling schools will counteract selection bias. Second, we will use previously validated and contextually appropriate instruments and thorough training of interviewers to counteract potential reporting biases and validity threats. Third, persons involved in collecting data will remain blind to the treatment conditions of the schools as the allocation to intervention and control group will be executed at the cluster level by research team members not collecting data. Fourth, carrying out analyses of data on the level of groups as randomized (intent-to-treat) will avoid incomplete accounting of participants and outcome events.

#### Ethical considerations

To protect participants’ identity, pseudonymization of collected research data will be ensured by creating a random participant code and the use of separate databases. The assignment of data from different assessment points, which is necessary due to the longitudinal study design, will be completed using the participant codes. All content collected or discussed during the investigation will be kept strictly confidential. After the completion of data collection and data quality checks, data will be fully anonymized.

As behavioral intervention studies are minimum risk studies, adverse events as a consequence of the intervention itself are not expected for our study. However, participants will be asked about personal experiences with child maltreatment, the use of or exposure to violence, their stress, and problematic family relations. This information is of intimate nature and may be perceived as stigmatizing. Participants will be protected by keeping all information confidential. Due to the interview’s content on violence, participants may be placed under mental strain depending on the burden of traumatic or aversive events and mental symptoms. High stress can lead to negative memories, emotions and physical reactions, concentration difficulties, and feelings of fatigue. In addition, it can be assumed that participants with traumatic and aversive experiences and mental symptoms are no less confronted with negative thoughts, feelings and memories in their daily experience than during the interview. Participants will be informed about the content of questions prior to the interview. Awareness about the possible occurrence of unpleasant feelings and emotions will be raised. In case participants experience severe psychological stress during the interview, short-term psychological support will be offered immediately.

## Data analyses

### Quantitative outcomes

To statistically investigate the study’s main research question whether ICC-T and ICC-P have a decreasing effect on teachers’ and parents’ use of violence against children in home and school settings, interaction effects of time*intervention will be modeled on the primary outcomes of teachers’ and parents’ violence use against children reported by teachers, parents and children respectively in mixed models for repeated measures accounting for cluster effects of participants’ nested in school. Secondary outcomes will be analyzed for potential time*intervention with mixed models. In case of significantly (*p* < 0.05) zero-inflated outcomes, model approaches for non-normally distributed data (e.g., Poisson, negative binomial) will be used. In case of unstable models due to potential outliers, variables will be winsorized (quantiles 5% & 95%) for model robustness. In case of missing data at random, multiple imputation methods will be used. Models will be corrected for multiple testing. In addition to the main inferential analyses, the prevalence of maltreatment and violence in different settings as well as children’s mental health and well-being from baseline assessment data will be captured based on descriptive statistics. Results will be presented including appropriate effects sizes and with a measure of precision (95% confidence intervals). Effect size of η^2^ ≥ 0.01, η^2^ ≥ 0.06, η^2^ ≥ 0.14 will be considered representing a small, moderate, and large effect, respectively [96].

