## Methods

### Design

We will use a two-armed school-based CRCT including 16 primary schools in the region of Morogoro, Tanzania. Eight of 16 selected schools will be randomly allocated to the intervention group, which will receive the school-based training (ICC-T for teachers, ICC-P for parents), and the other eight schools will be allocated to the control group without any intervention. The study will include two data collection phases, one baseline assessment before the intervention allocation and one follow-up assessment approximately three months after the allocation and delivery of the intervention (c.f., study flow chart in Fig. 1 & time-line in Table 1).

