### Study setting and sampling

This intervention study will be implemented in public primary schools in Morogoro in Eastern Tanzania, particularly in the urban district of Morogoro. Based on geographical locations of districts in the Morogoro region, the Morogoro urban district council was purposely selected for the study for feasibility reasons. For randomization, we used random.org [54]. First, we created a list of all eligible schools (38) fulfilling our inclusion and exclusion criteria from all wards (smallest administrative unit) located within the urban district of Morogoro. Second, based on our a priori power analysis, we randomly selected 16 wards and one school in each ward. We selected one school from each ward to avoid cross-over effects between the study conditions due to proximity of schools. Third, pairs of schools were formed due to primarily logistical reasons: Due to the short funding period (12 months) of this research project, the intervention will be delivered school by school. Once the first pair of schools has completed the baseline assessment, the random allocation assigns one school to the intervention and the other to the control condition and the implementation of the intervention starts directly after allocation. The allocation of the schools will be performed by the research team witnessed by two teachers from each school.

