*A priori* sample size and power analyses using The Shiny CRT Calculator [55] for the CRCT with pre-post assessment was conducted [56] with a critical significant level of 5%, a power of 80%, an expected moderate effect size of ƒ = 0.25, and an assumed intra-class correlation coefficient of .05. Previous ICC-T trials in Tanzanian secondary schools revealed moderate to large effects on student-reported and teacher-reported violence by teachers, respectively [3, 4, 39, 53]. Assuming no dropout at the school level and accounting for potential dropout on the participant level of 25%, and eight clusters per arm, 25 to 28 participants within a cluster would result in sufficient power. To account for parents’ response rates that are expected to be lower than 100%, parents from 45 randomly selected students will be invited to participate. Based on an expected approximated 85% response rate of invited mothers and 65% of invited fathers, 38 mothers and 29 fathers are assumed to participate in the study. In addition, 25 teacher per school will be included in the present study. This results in a sample size of 720 students, 608 mothers, 464 fathers and 400 teachers across 16 schools. Based on these assumptions, an *a priori *power of ß = .94 for students, for mothers ß = .90, for fathers ß = .82, and ß = .76 for teachers was calculated.

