### Outcomes

Quantitative data will be collected to investigate the effects of ICC-T and ICC-P on the teachers’ and parents’ use of violence against children in home and school. As primary quantitative outcome, violence by teachers in school and by parents at home will be assessed. The secondary quantitative outcome measures include parents’ and teachers’ favorable attitudes towards violence, children’s mental health problems, children’s quality of life, peer violence experienced by children, parent–child relationship and teacher–child relationship, perceived stress of all participants, school climate experienced by teachers, teachers’ self-efficacy, teachers’ decision making, teachers’ and parents’ normative beliefs about violence, and intimate partner violence experienced by female parents. All primary and secondary quantitative outcomes will be collected at baseline and follow-up data assessment. In addition, socio-demographic data on participants’ age, gender, and living situation will be assessed. Apart from this, children will be asked to identify the two most caring persons for them personally and parents and teachers will be asked on their household earnings.

Qualitative information will be collected to complement the quantitative data with FGDs and in-depth interviews for process evaluation and qualitative end-line evaluation. A process evaluation will be conducted to assess the quality and fidelity of the implementation of the intervention, participants’ engagement with the intervention, and whether the intervention achieved its goals in terms of its primary and secondary quantitative outcomes. The FDGs will assess the parents’ and teachers’ experiences with and thoughts on the intervention. The in-depth interview will assess parents’ and teachers’ perceived improvement of violence reduction. For qualitative information on process evaluation, standardized evaluation as well as reflection forms will assess the staff members’ experiences with conducting the intervention.

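### The primary time-by-intervention test is valid but gives away precision that the pre-allocation baseline scores could supply

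*Protocol article*

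**What the plan says.** Under Data analyses, Quantitative outcomes, the article fixes the primary test: "interaction effects of time*intervention will be modeled on the primary outcomes of teachers’ and parents’ violence use against children". It names the type of model as well: "in mixed models for repeated measures accounting for cluster effects of participants’ nested in school". It mentions neither a baseline covariate nor a common baseline mean.

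The Design section gives two assessments: "one baseline assessment before the intervention allocation and one follow-up assessment approximately three months after the allocation and delivery of the intervention". Study setting and sampling confirms the order within each pair of schools, one school going to each arm: "Once the first pair of schools has completed the baseline assessment, the random allocation assigns one school to the intervention and the other to the". The Outcomes section adds: "All primary and secondary quantitative outcomes will be collected at baseline and follow-up data assessment".

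The sample-size text under Participants assumes "a critical significant level of 5%, a power of 80%, an expected moderate effect size of ƒ = 0.25". For clustering within schools it takes "an assumed intra-class correlation coefficient of .05", with eight schools per arm and 25% participant dropout. It reports "an *a priori *power of ß = .94 for students, for mothers ß = .90, for fathers ß = .82, and ß = .76 for teachers was calculated". It gives no correlation between baseline and follow-up.

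**The concern.** With a single follow-up, a time-by-intervention term exists only if baseline is one of the two outcome occasions. On the ordinary reading, with both main effects in the model, the interaction subtracts the whole observed baseline difference between arms. Allocation comes after baseline, so that difference is chance alone. Estimating it freely and subtracting it in full adds noise unless school means are almost perfectly correlated over time.

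What is at stake is precision. Only 16 schools are randomised. The stated power for teachers (.76) is below the article's own 80% target, and that for fathers (.82) is only just above it. The baseline scores that could help are already being collected.

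**Working it through.** **Inputs.** From the Participants section: 8 schools per arm; 45, 38, 29 and 25 students, mothers, fathers and teachers per school; intra-class correlation .05; 25% dropout; f = 0.25, which is d = 2f = 0.5 for two equal groups; alpha 5%, taken as two-sided. Assumed, because not given: r, the correlation of a school's baseline and follow-up means.

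**1. The stated powers.** A follow-up-only comparison uses DE = 1 + (m − 1) × .05 and SE = √(2·DE/(8m)). For teachers after dropout, m = 18.75, so DE = 1.8875, SE = 0.159 and power = Φ(0.5/0.159 − 1.96) = .883. For students, mothers, fathers and teachers:

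| Basis | Students | Mothers | Fathers | Teachers |
|---|---|---|---|---|
| Stated | .94 | .90 | .82 | .76 |
| Normal | .947 | .934 | .904 | .883 |
| t, 14 df | .914 | .896 | .859 | .834 |

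Neither row matches all four. An unconstrained pre-post contrast with an unreported school autocorrelation of 0.85 and individual autocorrelation of 0 (d = 0.5, 25% dropout, t with 13 df) gives .933/.898/.823/.773, within 2 points. At d = 0.25 with a high individual correlation, both the change contrast and a baseline-adjusted analysis can match. The stated inputs therefore do not show which test the powers describe.

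**2. Variances.** Let v be the variance of one school mean on one occasion.

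- Change contrast: (2v/8) × 2(1 − r)
- Baseline-adjusted or common baseline, slope known: (2v/8) × (1 − r²)
- Ratio: (1 − r²)/[2(1 − r)] = (1 + r)/2

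| r | 0.3 | 0.5 | 0.7 | 0.9 |
|---|---|---|---|---|
| Variance ratio | 0.65 | 0.75 | 0.85 | 0.95 |

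Below r = 0.5 the factor 2(1 − r) exceeds 1, so the change contrast is less precise than ignoring baseline altogether.

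**3. Cost of estimating the slope.** With 16 school means there are 14 within-arm degrees of freedom. Estimating the slope inflates the adjusted variance on average by 1 + 1/(14 − 2) = 13/12. The advantage is gone when (13/12)(1 + r)/2 = 1, that is r = 24/13 − 1 ≈ 0.85.

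Simulation of 16 school means (20,000 runs per row; teachers, 18.75 per school, d = 0.5) agrees:

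| r | Power, interaction | Power, adjusted |
|---|---|---|
| 0.35 | .73 | .85 |
| 0.50 | .84 | .90 |
| 0.60 | .90 | .94 |
| 0.70 | .96 | .97 |
| 0.80 | .996 | .996 |

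Mean estimates were 0.50 for both methods in every row, so neither is biased.

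**4. If the stated powers are those of the interaction test.** For teachers, z = 0.706 + 1.960 = 2.666.

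- r = 0.5: 2.666/√0.75 = 3.078, power .87 (t, 13 df: .86)
- r = 0.7: 2.666/√0.85 = 2.892, power .82 (t, 13 df: .82)

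For fathers, the t figures are .91 and .87. These treat the slope as known. Applying the simulated variance ratios with the slope estimated (0.804 and 0.912), teachers reach about .84 (2.666/√0.804 − 1.96 = 1.01) and .80 (2.666/√0.912 − 1.96 = 0.83).

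**The case against.** **The sentence does not write out the fixed effects.** A model with time and time-by-intervention but no intervention effect at baseline also tests an interaction, so the text could accommodate the better analysis, and an analysis plan might specify it. This stands in part: a reader might infer that the article rules out a common baseline, and it does not. But an unqualified interaction in a repeated-measures model would ordinarily be fitted with both main effects, and anyone following the text would get the less precise test.

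**The power gain is not established.** It depends on an unreported r and on whose power was calculated. If the stated powers already assume efficient use of baseline, applying the ratio to them counts the gain twice. At the stated d = 0.5 with r = 0.5 and 25% dropout, the normal formula gives teachers .883 against .953, so both analyses exceed 80%. This stands. The variance ratio does not depend on d or on the stated powers; the power figures are illustrations.

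**There is a scientific interest in change.** The Discussion expresses interest in change within participants and between conditions. That explains the choice, but a common-baseline model also estimates change in each arm.

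**Bias.** A reader might infer that the change contrast is biased because, given an observed baseline imbalance, it over-corrects. The protocol does not support this. Allocation is random, so the imbalance averages to zero; the conditional over-correction is the same loss of precision seen from another side.

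**Scope of the formula.** It is for linear models. The article also allows Poisson or negative binomial models and allocates within pairs of schools. The principle carries over, but the exact figures may not.

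**Conclusion.** The point holds as one of efficiency. On the ordinary reading, the primary test is the between-arm difference in mean change: valid and unbiased over randomisation, but less precise than a baseline-adjusted analysis for most plausible r. The saving in variance is 35% at r = 0.3, 25% at 0.5, 15% at 0.7 and 5% at 0.9 with the slope known. In practice it is close to nothing above about r = 0.8. It matters most for teachers, where it might lift the comparison to the 80% target, but that rests on the unproven assumption that .76 is the power of the interaction test. The documents do not show that the stated powers are wrong or that the teacher comparison is underpowered for this reason. Label: free or cheap improvement, not an error in validity.

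**What to change.** In Data analyses, Quantitative outcomes, make the primary test baseline-adjusted, by one of two routes:

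- (a) Keep the repeated-measures mixed model and the time-by-intervention term, but constrain the arms to a common baseline mean (no intervention main effect at baseline), with school and school-by-time random effects. Participants with baseline only still contribute.
- (b) Model the follow-up score on intervention, the participant's own baseline score and the school-mean baseline score, with a school random effect.

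Use small-sample degrees of freedom suited to 16 schools, and keep the unconstrained interaction as a sensitivity analysis. Settle the choice before follow-up data are analysed, so that it cannot depend on which result looks better.

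The cost is a change of wording, with no new data or participants. The downside is about one school-level degree of freedom if the school-mean baseline is added, and little gain if r is high.

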#### Primary quantitative outcomes

##### Parental violence

The use of emotional and physical violence by parents against children at home will be measured with adapted versions of the Conflict Tactics Scale (CTS) [3, 63, 64], on the one hand by children’s self-reported violence experiences and on the other hand by parents’ self-report on the use of violence. For the present study, the CTS will include 9 items on experienced physical violence, 7 items on experienced emotional violence, and 5 items on emotional maltreatment. The items will be answered on a 7-point Likert scale ranging from 0 (this has never happened in the past week) to 6 (not past week, but before). CTS-scores on emotional and physical violence will be derived by summing up the respective item scores, whereby higher scores indicate higher levels of parental violence. A previous study in Tanzania assessed parental violence with the adapted CTS versions and revealed good psychometric properties [53].

In addition, during the quantitative interview 4 CTS-items will be body mapped by asking the children where on their body they experienced the emotional (shout & call dumps) and physical (hit & slap) violent act by parents. The affected body parts will be documented on a sheet of paper with a body-icon. Promising results for body mapping have been shown for trauma research in the context of refugees [65].

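### A zero-inflation p-value can replace the primary model with Poisson, which handles neither excess zeros nor overdispersion, and conditional winsorizing shrinks the effect

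*Protocol article*

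**What the plan says.** All of this stands in the Protocol article, Data analyses, Quantitative outcomes, unless noted.

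- **Default.** Time-by-intervention effects on the primary outcomes are estimated in "mixed models for repeated measures accounting for cluster effects of participants’ nested in school". I read this as a linear model, since the alternatives offered are for non-normal data and effects are graded by η².
- **First override.** For significantly (p < 0.05) "zero-inflated outcomes, model approaches for non-normally distributed data (e.g., Poisson, negative binomial) will be used". Both models are examples, and nothing decides between them.
- **Second override.** "In case of unstable models due to potential outliers, variables will be winsorized (quantiles 5% & 95%) for model robustness". The section does not keep an unwinsorized result as the primary one.
- **Effect size.** The same η² thresholds (0.01, 0.06, 0.14) apply whichever model is used.
- **Score (Outcomes, Parental violence; the teacher version uses the same scale and scoring).** "CTS-scores on emotional and physical violence will be derived by summing up the respective item scores". Items use a "7-point Likert scale ranging from 0 (this has never happened in the past week) to 6 (not past week, but before"), so nine physical items give a maximum of 9 × 6 = 54.

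**The concern.** Both overrides act on the primary outcomes, and the article states them as rules.

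The first one does not match trigger to remedy. Poisson adds nothing for excess zeros, and it forces the variance to equal the mean. The outcome is a sum of graded codes, not an event count, so that equality has no basis here. If the variance exceeds the mean within persons, the Poisson standard error is too small and the trial can report an effect that is not there.

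The switch also changes what is estimated. The default interaction is a difference of mean changes; under the usual log link it becomes a ratio of ratios, for which η² has no standard definition. The rule is applied to each outcome, so reports by children, parents and teachers could end on different scales.

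The second override changes the scores themselves. It pulls in the upper tail and so attenuates a real effect.

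**Working it through.** The plan gives no mean, variance, share of zeros or error rate for the violence scores, so there is no figure of its own to reproduce here. The stated power figures do not enter this point. Everything below is illustration under stated assumptions.

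**1. Why a sum of codes need not have variance equal to mean.** Take n independent items, each scored k with probability p and otherwise 0. The mean is nkp and the variance nk²p(1−p), so variance/mean = k(1−p). With k = 3 and p = 0.2 (assumed) this is 3 × 0.8 = 2.4. Many zeros mean low p, so codes above 1 tend to push the ratio above 1 just where this branch is used.

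**2. Size of the Poisson error.** Let φ be the variance/mean ratio left within persons. The Poisson standard error is too small by the factor 1/√φ, so for a nominal two-sided 5% test

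type I error = 2 × (1 − Φ(1.96/√φ)).

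| φ (assumed) | 1.96/√φ | Type I error |
|---|---|---|
| 1 | 1.960 | 5.0% |
| 2 | 1.386 | 16.6% |
| 3 | 1.132 | 25.8% |
| 4 | 0.980 | 32.7% |

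**3. Does a participant random effect rescue Poisson?** Simulated null trials had 16 schools with 34 participants each (45 less 25% dropout = 33.75), two visits, scores capped at 54 and no school-by-time variation. Assumed means were 3 or 8, with visit-level gamma variation and 0 or 20% extra zeros. Both models had a participant random intercept and used a likelihood-ratio test, with 200 runs per row.

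| Mean | Gamma shape | Extra zeros | Poisson | Negative binomial |
|---|---|---|---|---|
| 3 | 4 | 0 | 21% | 5.5% |
| 3 | 2 | 0 | 27.5% | 4% |
| 3 | 2 | 20% | 35% | 4.5% |
| 8 | 2 | 20% | 48.5% | 1% |

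The Monte Carlo standard error at 5% is √(0.05 × 0.95/200) = 1.5 points. The random intercept absorbs differences between persons, but not variation between visits of the same person. Over a wider grid (means 3–15, 2,000 runs), a Gaussian change-score test gave 4.4–5.8% and a school-level t-test with 14 degrees of freedom gave 4.3–5.8%. With no within-person overdispersion, Poisson held 5.0%.

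**4. The trigger.** A zero-inflation score test with Poisson as reference fired in 100% of runs, including data with no structural zeros. With that reference the test detects overdispersion, and it then permits Poisson just when the data have rejected it. Another test or reference could behave differently.

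**5. Winsorizing.** Estimated change under a true 30% reduction, difference scale:

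| Mean | Gamma shape | Unwinsorized | Winsorized | Share kept |
|---|---|---|---|---|
| 3 | 1 | −0.90 | −0.68 | 0.76 |
| 8 | 4 | −2.39 | −2.02 | 0.84 |
| 15 | 2 | −3.92 | −3.69 | 0.94 |

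Over all overdispersed scenarios the shrinkage was 6–24% on the difference scale and 4–16% on the log-ratio scale. Where at least 5% of scores are zero, the lower cut does nothing and only the upper tail is clipped.

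**The case against.** The strongest reply is that the list of models is open and already names negative binomial, which controlled the error rate in the check above. The section never says that the random effects are dropped. A reader might infer that the plan prescribes a plain Poisson model; the text does not support that. The standard-error problem belongs to one permitted branch. What remains is that Poisson is permitted, with nothing to steer the analyst away from it.

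Second, the percentages depend on dispersion that the documents do not report, and they apply only to what is left within persons. This stands, and the figures are offered only as a range.

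Third, a reader might infer that choosing the model by p-value itself inflates the error. This was not shown: the trigger always fired, so the inflation came from the Poisson variance. Nor does the section say that the choice would be made with treatment arms known. The objection to the switch is the change of effect scale and the route to Poisson.

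Fourth, a reader might infer that winsorizing trims the most severe violence. The printed scale does not support that. Its top code, 6, means that the act occurred before the past week but not in it, so a high score need not mean severe recent violence. Winsorizing is also conditional, and it shrinks effects rather than creating false positives.

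Last, the unnamed zero-inflation test and the undefined instability are details that a condensed article may leave to the full plan. They are not part of this point.

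**Conclusion.** The point holds in a limited form and is worth correcting before analysis. The article lets a significance test on the outcome replace the default model and change the effect scale, and it permits Poisson, which suits neither excess zeros nor overdispersion.

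If Poisson is used and variance/mean within persons is 2 to 4, the nominal 5% test has a true level of about 17–33%. Under the simulated conditions it was 21–48.5% with a participant random effect, against 1–5.5% for negative binomial. If no such overdispersion exists, the harm disappears.

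The winsorizing part does not depend on Poisson: a true 30% reduction loses roughly 6–24% on the difference scale under the assumed distributions. The simulations had no school-by-time variation, so the good results for the alternatives concern overdispersion only; school clustering must still be handled.

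**What to change.** - Delete Poisson, and remove the zero-inflation p-value as a switch.
- Name one primary model and one effect scale for all violence scores, with a variance valid under overdispersion and school clustering. The simplest choice is the linear mixed model already stated, with cluster-level degrees of freedom, and negative binomial as a sensitivity analysis. This also keeps all informants on one scale and the η² grading interpretable.
- If a distributional choice is still wanted, make it on baseline data or on data blinded to arm.
- Analyse unwinsorized scores as primary, and report winsorized results as a sensitivity analysis.

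The cost is a few sentences of analysis wording, with no change to design or data collection. The downside is slightly less flexibility if the named model fits poorly.
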